**Potential mechanism variables**			
	Affect	5 items, shortened from [53]	Momentary
	Sleep	2 items, as in [53]	Last night^f^
	Catastrophizing	4 items, as in [21,53]	Last week
	Partner communication	3 items, based on [21]	Last week
	Partner interactions	6 items, shortened from [20]	Last week
	Self-efficacy	3 items, based on the SES^g^	Last week
	Mindfulness	4 items, based on the FMI^h^	Last week
	Closeness	2 developed items	Last week

^a^Patient only.

^b^Items ask the participants to report their current state (eg, “How fatigued do you feel right now?”).

^c^Partners report on their perception of patients’ fatigue.

^d^SFQ: Short Fatigue Questionnaire [54].

^e^Items ask the participants to report their state from the previous week.

^f^Items ask the participants to report their state from the previous night.

^g^SES: Self-Efficacy Scale [44].

^h^FMI: Freiburg Mindfulness Inventory Short Form [46].

Weekly fatigue severity in patients will be assessed with the 4-item Short Fatigue Questionnaire (SFQ) [54], a shortened version of the CIS-fatigue. The time frame has been adapted from the original past 2 weeks to the previous week, and items are formulated in the past tense (eg, “I felt tired”).

Current fatigue severity will be assessed in the weekly diaries with 1 item, “How fatigued do you feel right now?” that is scored on an 11-point Likert scale ranging from (score 0) “not at all” to (score 10) “as fatigued as I could be” [20,21,53].

### Analyses

Analyses will be conducted in SPSS (IBM Corp) and Mplus (Muthén & Muthén).

#### Descriptive Statistics

Descriptive statistics will be presented in a table. Data for patients with cancer and their partners will be presented separately (with the exception of couple characteristics such as relationship status). A study flowchart will show the number of couples screened, eligible, and included, as well as reasons for noneligibility and dropout.

#### Benchmark and Critical Values

This pilot trial is designed to assess the acceptability, potential efficacy, and potential working mechanisms of COMPANION and to determine the feasibility of trial procedures. To establish whether a subsequent randomized controlled trial (RCT) is justified, we have set benchmarks and critical values. Benchmark values represent the lower values of what we deem desirable to achieve. Critical values are defined as half of the benchmark values and represent potential problems with the outcome assessed. These benchmarks and critical values are based on comparable literature and our clinical and research experience. As each trial is unique (eg, in terms of study design, target population, intervention content, and duration), benchmark values are set rather conservatively (ie, similar to or lower than in comparable studies). The benchmark and critical values will not serve as definitive thresholds to determine whether a larger RCT is justified but will be interpreted along with the other outcomes, focus group data, and the recruitment log. Table 4 provides an overview of the key outcomes, their operationalizations, benchmark, and critical values.

**Table 4 table4:** Overview of outcome measures, their operationalizations, benchmark, and critical values.

Outcome		Operationalization	Data	Benchmark values	Critical values
**Acceptability of COMPANION**					
	Intervention adherence	Percentage of couples in which the patient completed the intervention, that is, followed at least 6 out of 9 sessions, and the partner did not drop out	T1 (patients) and/or therapist log	≥60% of couples completed the intervention	<30% of couples completed the intervention
	Intervention satisfaction	Percentage of patients and partners responding to T1 who are satisfied with the couple approach and the intervention overall (score ≥5 on a 7-point Likert scale)	T1 (patients and partners)	≥70% of patients and ≥70% of partners are satisfied with the intervention overall and/or the couple approach	<35% of patients and <35% of partners are satisfied with the intervention overall and/or the couple approach
**Potential efficacy for patient fatigue**					
	Significant change in patient fatigue	Statistically significant decrease from CIS-fatigue_T0_^a^ to CIS-fatigue_T1_ (intention-to-treat).	T0 and T1 (patients)	Significant improvement in patient fatigue (*P<*.05, intention-to-treat)	N/A^b^
	Clinically relevant improvement	Percentage of patients in which CIS-fatigue_T0_–CIS-fatigue_T1_≥6.	T0 and T1 (patients)	≥45% of patients improved (intention-to-treat)	<23% of patients improved (intention-to-treat)
**Feasibility of trial procedures**					
	Rates related to the recruitment procedure	Recruitment rate: average per month, averaged across recruitment strategies.	Recruitment log	≥3 couples included per month	<1.5 couples included per month
	Adherence to the T1 and T2 questionnaires	Percentage of patients and partners completing and returning T1 and T2.	T1 and T2 (patients and partners), recruitment log	≥65% of patients and partners completed T1 and ≥60% of patients and partners completed T2	<33% of patients and partners completed T1 and <30% of patients and partners completed T2
	Adherence to the diary protocol	Percentage of diaries completed by patients and partners.	Diary (patients and partners), recruitment log	≥65% of diaries completed by patients and partners	<33% of diaries completed by patients and partners
**Potential working mechanisms**					
	Changes in fatigue and potential mechanisms over time	Co-occurrence of time slopes of potential mechanisms with time slope of fatigue.	Diary (patients)	Targeted cognitions and behaviors improve (ie, time slopes are significantly different from 0); improvements co-occur with improved fatigue (standardized covariance is significant, *P*<.05)	N/A

^a^CIS-fatigue: Checklist Individual Strength, subscale Fatigue Severity.

^b^Not applicable.

#### Primary Aims

Acceptability of the couple intervention will be determined in terms of adherence to and satisfaction with the couple intervention. The benchmark value for adherence is based upon the rates of the trial that tested the patient-centered intervention (ie, 38% of intervention dropout [31]) and on comparable web-based couple interventions [55,56]. Couples will not be considered in cases where the investigator decides to withdraw the couple or a change in health status occurs that interferes with participation. The benchmark value for satisfaction is based upon the couple intervention trial by McDonnell et al [40], in which acceptability with different intervention components ranged between 75% and 100% for patients and family members.

The potential efficacy of the couple intervention will be determined in terms of a statistically significant decrease and a relevant improvement (≥6-point decrease on CIS-fatigue) in patient fatigue between T0 and T1. Both intention-to-treat analyses (ie, including all couples allocated) as well as per-protocol analyses (ie, including only couples who completed COMPANION as defined above) will be performed. The benchmark value for the percentage of clinically relevant improvement is based on our previous trial, in which 49% of the patients allocated to patient-centered eMBCT benefitted in terms of reduced fatigue (intention-to-treat; using a stricter criterion to define improvement as used here) [31].

Missing values will be replaced with multiple imputations using chained equations. The imputation model will include demographic and clinical variables as assessed at baseline. In sensitivity analyses, completer analyses will be performed (ie, including only cases with nonmissing CIS-fatigue_T0_ and CIS-fatigue_T1_ values). Of note, the study evaluating the patient-centered intervention included only curatively treated patients. It might be that the formulated benchmark values for efficacy are too strict for patients with cancer recurrence or reinitiation of treatment. If applicable, we will therefore calculate the efficacy outcomes with and without these patients included.

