### Sample Size Calculation

The study is powered to test the potential efficacy of the couple intervention in reducing patient fatigue (ie, the second primary research aim). Patients’ baseline (T0) and postintervention (T1) scores on the Checklist Individual Strength, subscale Fatigue Severity (CIS-fatigue) will be analyzed with a 1-tailed matched pairs *t* test. G*Power analysis indicated that 27 patients are required to detect a medium effect (0.5) with an α of .05 and a power of 0.8 (1-tailed). We expect CIS-fatigue scores at T1 to be significantly lower than CIS-fatigue scores at T0. We will conduct a 1-sided test given the gain in power as compared to a 2-sided test and evidence that an increase in mean fatigue is unlikely to occur [31]. Based on the drop-out rate in our previous trial [31] and a recent review of the attrition rate in couple-based interventions for cancer [36], we assume a 20% drop-out rate. Hence, we will aim to include a total of 34 couples.

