**Other relevant measures**							
	Emotional well-being	HADS^m^		✓	✓	✓	
	Relationship satisfaction	MMQ-marital satisfaction^n^		✓	✓	✓	
	Caregiver burden regarding patient fatigue^o^	ICQ^p^, partner version		✓	✓		
	Perceived change in fatigue^f^	Developed item based on [41]			✓		
	Adverse events	Developed items based on [41], self-report and therapist or recruitment log			✓		
	Supportive care use for mental health issues	Developed items based on [41]		✓			

^a^Some screening items will be assessed verbally on the phone (eg, relationship status), others through a questionnaire (eg, fatigue items).

^b^T0 is baseline.

^c^T1 is 2 weeks after completion of the intervention.

^d^T2 is 1 month after T1.

^e^FG: focus group.

^f^Patient only.

^g^CCRF: chronic cancer-related fatigue.

^h^For partners at baseline and T1 only.

^i^CIS-fatigue: Checklist Individual Strength, subscale Fatigue Severity [42,43].

^j^SES: Self-Efficacy Scale [44].

^k^J-FCS: Jacobsen Fatigue Catastrophizing Scale [45].

^l^FMI: Freiburg Mindfulness Inventory Short Form [46].

^m^HADS: Hospital Anxiety and Depression Scale [47,48].

^n^MMQ: Maudsley Marital Questionnaire, subscale Marital Satisfaction [49,50].

^o^Partner only.

^p^ICQ: Illness Cognition Questionnaire [51].

Demographic characteristics will be assessed at the screening and T0 and include self-reported age, sex, level of education, occupational status, relationship status and duration, cohabitation status and duration, and comorbidities.

Patients’ cancer-related variables are self-reported and include cancer type, prognosis, presence of metastasis, treatment received, time since diagnosis, and time since treatment completion.

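### The imputation predictors named for T1 fatigue are baseline variables and omit weekly diary fatigue; if non-improvers miss T1 more often, the ITT result is overstated and the completer analysis would not show it

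*Protocol article*

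**What the plan says.** Under Primary Aims, the protocol article fixes the method, "Missing values will be replaced with multiple imputations using chained equations", and then the content of the model: "The imputation model will include demographic and clinical variables as assessed at baseline". No post-baseline variable is named, no number of predictors is given, and it is not said whether T0 CIS-fatigue counts as clinical. The one check on missing data is this: "In sensitivity analyses, completer analyses will be performed", restricted to patients with both T0 and T1 scores. Table 4 labels both efficacy benchmarks (the significance test and the 45% responder figure) as intention-to-treat, which Primary Aims defines as all allocated couples.

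Other sections show what else is collected. Under Measures: "Weekly fatigue severity in patients will be assessed with the 4-item Short Fatigue Questionnaire (SFQ) [54], a shortened version of the CIS-fatigue". Diaries run from a week before the intervention to a week after it, 17 to 22 weeks in all (Table 3). The therapist log records the session after which a patient stopped. Table 2 has patients completing CIS-fatigue at T2. Under Secondary Aims, the diaries serve the mechanism analysis; Primary Aims gives them no role in imputation.

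**The concern.** An imputation model protects against selective dropout only as far as its predictors explain both the missing outcome and the reason it is missing. Baseline characteristics say little about how a patient fared during 15 to 20 weeks of treatment. Weekly fatigue says much more, because it is measured on part of the primary scale. If it is left out, a patient whose fatigue stayed high and who then failed to return T1 is imputed as if he or she had changed like responders to T1 with similar baseline values.

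The completer analysis drops such patients, which amounts to much the same assumption. Agreement between the two analyses would then look like robustness without being evidence of it. At stake are the second primary aim and the 45% benchmark, which feed the judgement on proceeding to a randomized trial.

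A separate question is model size. Measures lists 9 demographic and 6 cancer-related variables. Entering all or most of them on the few observed T1 scores would cost precision.

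**Working it through.** **The plan's own figure.** The test is one-sided and paired: T0 and T1 scores "will be analyzed with a 1-tailed matched pairs *t* test". With d = 0.5 and α = .05, the noncentrality is 0.5 × √27 = 2.598 on 26 df, giving power 0.812; n = 26 gives 0.798. So 27 reproduces. With "we assume a 20% drop-out rate", 27 / 0.8 = 33.75, rounded up to 34. This also reproduces.

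**How many outcomes would be imputed.** Three figures in the article bear on this:

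| Source | T1 observed | Of 34 | To impute |
|---|---|---|---|
| Sample Size Calculation, 20% drop-out | 80% | about 27 | about 7 |
| Secondary Aims, previous trial | 73% | about 25 | about 9 |
| Table 4, T1 adherence benchmark | 65% | about 22 | about 12 |

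**Simulation of the imputed effect.** Trials of 34 patients, 1,000 per scenario; Bayesian linear-regression imputation of T1 change; 30 imputations; Rubin pooling with small-sample df. Effects are in SD of change. Assumptions not in the documents: diary change correlates 0.7 with T1 change, and where missingness is selective, the odds of missing T1 change by a factor of e per SD of diary improvement. T0 fatigue is taken to be in the model, the reading most favourable to the plan. Bias is given for a true effect of 0 and of 0.5; rejection is one-sided at .05 with a true effect of 0.

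| T1 missing more often in | Missing | T0-only imputation: bias; rejection | Completers: bias; rejection | T0 + diary: bias; rejection |
|---|---|---|---|---|
| Poor responders | 20% | +0.126, +0.132; 14% | +0.142, +0.145; 16% | −0.011, +0.009; 5% |
| Poor responders | 35% | +0.197, +0.184; 22% | +0.217, +0.196; 27% | +0.005, −0.006; 6% |
| Neither | 20% | +0.003, +0.001; 6% | +0.002, +0.004; 7% | −0.002, −0.004; 5% |
| Neither | 35% | −0.015, +0.003; 4% | −0.017, +0.010; 5% | −0.004, +0.008; 4% |
| Good responders | 20% | −0.127, −0.128; 1% | −0.143, −0.140; 1% | +0.003, 0.000; 4% |
| Good responders | 35% | −0.194, −0.215; 0.3% | −0.222, −0.228; 0.2% | +0.002, −0.010; 4% |

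Against the planned effect of 0.5, an upward bias of 0.13 to 0.20 SD is 26% to 40% (0.13 / 0.5; 0.20 / 0.5). The last column is a best case: the simulated missingness depends on the diary, and the diary is observed for everyone.

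**Translation to the responder benchmark.** Assume change is normal and the bias shifts its mean without altering its spread. A true responder rate of 43% (an illustrative value just under the benchmark) has z = −0.176. Then Φ(−0.176 + 0.13) = 48% and Φ(−0.176 + 0.20) = 51%, both above 45%.

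In counts: suppose 25 of 34 return T1 and 12 of them respond (48%). Imputing the other 9 at about that rate passes. The benchmark needs 0.45 × 34 = 15.3 responders, so it is truly missed if the 9 respond at less than (15.3 − 12) / 9 = 37%. If all 9 count as not improved, the rate is 12 / 34 = 35%.

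**Model size, with missingness unrelated to response.**

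| Predictors | SE, 20% missing | Power at d = 0.5 | SE, 35% missing | Power at d = 0.5 |
|---|---|---|---|---|
| T0 only | 0.19 | 0.81 | 0.22 | 0.69 |
| T0 + 15 single terms | 0.26–0.27 | 0.54 | 0.42–0.43 | 0.25 |
| T0 + diary | 0.19 | 0.83 | 0.20 | 0.77 |

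With T0 and 15 terms (16 predictors plus an intercept), residual df are 27 − 17 = 10 or 22 − 17 = 5. With 25 terms besides T0, as dummy coding might produce, the regression could be fitted in 43% to 48% of trials at 20% missing and in under 3% at 35%. Overfitting widens the interval and makes the test conservative (rejection under no effect of 2% to 3%). That is the opposite direction to the diary omission.

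**The case against.** The strongest reply is that the text is being read too narrowly. It says what the model will include, not that nothing else may enter, and a condensed article may leave auxiliary variables to a fuller plan. That stands against any claim that diary fatigue is excluded. It does not remove the point: the article chose to describe the predictors, confined the description to baseline, and named completers as the sole check.

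Second, a reader might infer that the ITT result is biased upward. The documents do not support that. Nothing in them shows that non-improvers are the ones who miss T1, and the table gives zero or downward bias under other mechanisms. Stopping treatment is also not the same as missing T1. In the previous trial 38% dropped out of the intervention, yet 73% completed T1 and T2. If the denominators are the same, at least 73 − 62 = 11% stopped and still supplied outcomes.

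Third, a reader might infer that the model is too large for 34 patients and the result very imprecise. The article gives no number of predictors. The list of 15 says what is collected, not what enters the imputation, and a small baseline model costs almost no precision. Imprecision is a risk only if most of the list is used.

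Fourth, the benchmarks are not decisive. Benchmark and Critical Values says they are not definitive thresholds, the Discussion weighs them with qualitative data, and the lack of a control arm is acknowledged. This stands, and it lowers the severity.

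Fifth, diaries may stop when the patient does, their completion benchmark is only 65%, and T2 may be lost with T1. This also stands: the added predictors reduce the problem and may not remove it.

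**Conclusion.** The point holds in conditional form. The named predictors are baseline variables, while better-placed predictors of a missing T1 are already collected and not named. If non-improvers miss T1 more often, the ITT mean change would be overstated by about 0.13 to 0.20 SD at 20% to 35% missing, with one-sided rejection under no effect of 14% to 22%. The completer analysis would be off by a similar amount (+0.14 to +0.22 SD) and so could not reveal it. These sizes rest on the assumed correlation of 0.7 and the assumed strength of selection; weaker values of either would shrink them.

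The loss of precision is a separate risk that arises only if most of the 15 baseline variables are entered. Because the benchmarks are advisory and the bias depends on an unknown mechanism, this is a cheap improvement and not a must-fix.

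**What to change.** Replace the sentence on the imputation model with a short, closed list:

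- CIS-fatigue at T0;
- a weekly SFQ summary, such as the last observed score or the mean of the last three;
- CIS-fatigue at T2 where available;
- sessions received, from the therapist log;
- at most one or two baseline covariates.

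Impute the CIS-fatigue score and derive the 6-point response from it. Keep the completer analysis and add a missing-not-at-random sensitivity analysis. For the 45% benchmark, one option is to count every missing T1 as not improved, presented as a conservative bound because it is itself biased downward.

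The cost is wording and a little more analysis; no new data are needed. The responder figure may become less favourable. Because diaries can end with dropout, the report should state how many patients missing T1 had recent diary scores.

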#### Secondary Aims

The feasibility of the trial procedures will be determined in terms of the recruitment rate. In our trial testing patient-centered eMBCT, on average, a total of 6 patients were included per month [31]. Given the known challenges in recruiting dyads for interventional research [36,57-59], the benchmark value is set lower, even lower than the number required (ie, 3,8) to reach our target sample size within the planned 9-month recruitment period.

The feasibility of the trial procedures will also be assessed in terms of adherence to the study protocol. In our previous trial, 73% of patients completed T1 and T2 [31]. In this trial, the follow-up period is shorter than in comparable trials (ie, 4 weeks). Still, given the intensity of the diary assessments (ie, up to 22 diaries), we set our benchmark value for completion of both assessments conservatively. In our observational diary study among fatigued survivors of cancer and their partners, compliance with the evening diary exceeded 90% [21]. While assessments in this study were also performed in the morning and noon, the diary period lasted only 2 weeks. It seems likely that the completion rate in this study is lower as the diary procedure is embedded in intensive treatment and the diary period covers several months; a study that had a diary duration of 6 months had a completion rate of 69% [60].

Based on the cognitive-behavioral model of fatigue and previous research [20,21,53,61], the potential mechanism variables are affect, sleep, catastrophizing, partner communication, partner interactions, self-efficacy, mindfulness, and closeness. A variable is established as a potential working mechanism of the couple intervention if its change (ie, improvement) over the course of the diary period covaries with decreases in weekly fatigue. Multilevel growth curve analysis will be applied to model the time slopes of the potential mechanisms and weekly fatigue over the entire diary period. We will explore both linear and nonlinear time trends and consider modeling random intercepts and random slopes. An improvement in fatigue and maladaptive constructs such as catastrophizing is indicated by a decrease over time. An improvement in adaptive constructs such as self-efficacy and mindfulness is indicated by an increase over time. For mechanism variables pertaining to partner communication and partner interactions, an improvement might be indicated by a decrease or increase. For some couples, talking (temporarily) more about fatigue is adaptive, while for others, talking (temporarily) less is adaptive. Covariances between the time slopes of the presumed mechanisms and the time slope of daily fatigue will be estimated to identify whether the temporal changes co-occur. A variable is established as a potential working mechanism in case the standardized covariance between the slope change factor for the outcome and that of the presumed mediators is significant (using a *z* test where ±1.96 is significant at the .05 level). Models will be run for weekly fatigue as well as weekly-reported momentary fatigue.

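### The working-mechanism rule under Secondary Aims tests only an unsigned slope covariance: it omits Table 4's mean-improvement condition and its own stated direction, and suits partner communication poorly

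*Protocol article*

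**What the plan says.** All references are to the protocol article.

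- **Definition (Secondary Aims).** A variable counts as a potential mechanism "if its change (ie, improvement) over the course of the diary period covaries with decreases in weekly fatigue". The section then gives directions: fatigue and maladaptive constructs should fall, adaptive constructs should rise.
- **Decision rule (same section, near the end).** "A variable is established as a potential working mechanism in case the standardized covariance between the slope change factor for the outcome". The other slope is the mediator's, and significance of the covariance is judged by a z "test where ±1.96 is significant at the .05 level".
- **Benchmark (Table 4, potential working mechanisms).** There are two conditions: "Targeted cognitions and behaviors improve (ie, time slopes are significantly different from 0"), and "improvements co-occur with improved fatigue (standardized covariance is significant" at .05).
- **Partner variables (Secondary Aims).** For partner communication and partner interactions, improvement may be a fall or a rise. The reason given concerns talking: "For some couples, talking (temporarily) more about fatigue is adaptive, while for others, talking (temporarily) less is adaptive". The same slope covariance is applied to these variables.
- **Outcome named in the covariance sentence.** Covariances with "the time slope of daily fatigue will be estimated". Table 3 describes a weekly diary, and the section closes by naming two fatigue outcomes, one for the past week and one momentary.

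**The concern.** Three statements of what makes a mechanism stand close together and do not agree. The definition has a direction. Table 4 adds a condition on the mean slope. The decision rule has neither, and it is the sentence an analyst would program. A covariance of slopes describes how couples differ from one another in their change. It says nothing about whether the average patient improved.

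The partner variables raise a separate difficulty. If more talking helps some couples and less talking helps others, one pooled, signed covariance mixes associations of opposite sign. Partner communication is central to the case for treating couples: the Introduction argues from daily partner interactions, and the Intervention section describes an added session on mindful communication. A null result produced by the form of the test could be read as evidence against that element. In the other direction, a variable could be reported as a mechanism on a result that contradicts the model.

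**Working it through.** **1. The plan's own figure.** 2 × (1 − Φ(1.96)) = 0.0500. The stated test is therefore two-sided, and a covariance of either sign passes.

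**2. The three statements side by side.**

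| Requirement | Definition, Secondary Aims | Decision rule, Secondary Aims | Table 4 |
|---|---|---|---|
| Mechanism improves on average | implied by the word improvement | not required | required, slope differs from 0 |
| Fatigue improves | yes, in words | not required | yes, in words |
| Sign of the covariance | implied | none | none |
| Significant covariance | not stated | required | required |

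The decision rule and Table 4 differ on mean improvement. On the sign of the covariance they share the same gap.

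**3. Size of the difference.** The documents give 34 couples planned and 27 patients after the assumed 20% drop-out (Sample Size Calculation). They give no slope correlation or mean slope, so these are assumptions: correlation 0.6 in absolute value, and mean slopes of 0 or 0.6 SD of the between-couple slope distribution. Method: 20,000 simulated trials, bivariate normal slopes observed without error, Fisher z test of the correlation at ±1.96, and t tests of both mean slopes. Table 4 read with direction means that both mean slopes improve significantly and the covariance is significant with the expected sign. Results are for n = 34, with n = 27 in brackets.

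| Assumed truth | Decision rule met | Table 4, direction required | Table 4, covariance left unsigned |
|---|---|---|---|
| Expected-sign covariance, no mean change | 97% (93%) | 0.6% (0.5%) | – |
| Wrong-sign covariance, both means improve 0.6 SD | 97% (93%) | 0% (0%) | 83% (65%) |
| Expected-sign covariance, both means worsen 0.6 SD | 97% (94%) | 0% (0%) | – |

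With no true covariance and no mean change, the decision rule is met in 5% of trials, about half of them with the wrong sign.

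**4. Partner communication.** Let A be a couple's adaptive change and F its fatigue slope. Let the recorded communication slope be S × A, where S = +1 with probability q (more talking is adaptive) and −1 otherwise, independent of A and F. Then

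Cov(SA, F) = E[S] × Cov(A, F) = (2q − 1) × Cov(A, F).

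With mean change 0, the variance of SA equals that of A. A correlation of 0.6 in size then becomes 0.6 × 0.6 = 0.36 at q = 0.8, 0.2 × 0.6 = 0.12 at q = 0.6, and 0 at q = 0.5. Simulation at n = 34:

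| q | Covariance significant in the majority direction, no mean change | Table 4 with direction, mean adaptive change 0.6 SD |
|---|---|---|
| 1.0 | 97% | 85% |
| 0.9 | 81% | 55% |
| 0.8 | 57% | 27% |
| 0.7 | 34% | 10% |
| 0.6 | 16% | 3% |
| 0.5 | 6% | 0.6% |

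At q = 0.5 the covariance is significant in about 13% of trials, divided evenly between the two signs, so the sign carries no information. Real slopes are estimated with error, so the detection rates in steps 3 and 4 are optimistic.

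**5. Daily fatigue.** The Assessments section and Table 3 provide for weekly diaries only. The two fatigue outcomes modelled are the past-week score and the momentary rating, both recorded weekly. No daily series exists, so the word is a slip.

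**The case against.** The strongest reply is that the section should be read as a whole. It opens by requiring improvement that covaries with falling fatigue and lists the directions, so a careful analyst would not call a wrong-sign result a mechanism. On that reading ±1.96 is only a critical value. This has force. A reader might infer that the plan accepts any significant covariance as proof of a mechanism, and the section as a whole does not say that. What remains is that the sentence stating when a mechanism is established does not carry out the definition beside it or Table 4's first condition.

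A reader might also infer that the test cannot detect partner communication at all. The documents do not support this. They give no split between types of couple, and under the assumptions above detection is 81% at q = 0.9 and 57% at q = 0.8. It is lost only near an even split.

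Nor does the cancellation argument carry over automatically to partner interactions. The couple-specific sentence concerns talking. The Introduction links facilitative reactions to better fatigue and solicitous ones to worse, so a fall or a rise may simply reflect different item types, each with a fixed direction.

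Finally, this is a secondary aim in a pilot. Benchmark and Critical Values says that the benchmarks are not definitive thresholds and are read with focus-group data. This limits the consequence. It does not remove the inconsistency, because the Discussion uses the benchmarks to inform the decision on a randomized trial.

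**Conclusion.** The point holds in a limited form. The decision rule is weaker than Table 4 on mean improvement, and neither place signs the covariance although the stated definition is directional. The two rules can give opposite answers on the same data: 97% against about 0.6% in the no-mean-change case. Leaving the covariance unsigned lets a wrong-direction result through even Table 4 in 83% of trials when both means improve by 0.6 SD. For partner communication the pooled covariance is attenuated by 2q − 1, so a null result should not be read as evidence against that mechanism.

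The table comparison and the two-sided reading rest on the text alone. Every simulated percentage rests on an assumed correlation of 0.6, assumed mean slopes, an assumed split and error-free slopes. The importance is moderate: worth correcting before analysis, with no bearing on the primary aims or the sample size.

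**What to change.** 1. **One rule in Secondary Aims and Table 4 for constructs with a stated direction.** Require all three: the mean mechanism slope differs significantly from 0 in the improving direction; the mean fatigue slope decreases; and the slope covariance is significant with the expected sign (negative with fatigue for constructs that should rise, positive for those that should fall).
2. **Partner communication.** Either take it out of this benchmark and report it descriptively, or prespecify an analysis that allows the adaptive direction to differ between couples and still addresses change over the course of therapy. State that precision will be low with 34 couples, and that a null pooled covariance is not evidence against the mechanism. A model of week-to-week coupling between communication and fatigue would answer a different question and is not a substitute.
3. **Partner interactions.** State the expected direction for each item type and apply rule 1 to each.
4. **Wording.** In the covariance sentence, replace daily fatigue with the two planned outcomes: weekly fatigue, and momentary fatigue as rated in the weekly diary.

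The cost is a few sentences and, if the second option in item 2 is taken, one extra analysis of diary data that are already planned. The signed three-part rule will be met less often than the present one, and that should be acknowledged.
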